### Sample size calculation

The required sample size is estimated using PASS v11.0 (NCSS, Kaysville, UT, USA) based on a completely random design for comparing the means of two independent samples. To our knowledge, there is no previous study on a stratified support pattern-based internet-assisted self-management therapy for DM-MCI in mainland China, so we estimate the effect size of one of the outcomes (HbA1c) based on previous research on patients with DM-MCI [42]. This study find that HbA1c scores in intervention and control group are 6.49 ± 1.59 and 6.97 ± 0.73, respectively. A sample size of 34 participants per group was determined to be sufficient to detect an effect with a type 1 error rate of 5% (α = 0.05) and 90% power (β = 0.1). A total of 68 participants will be needed, with 34 participants per group. Considering a 20% loss of follow-up rate, the final sample size is 86, with 43 participants per group.

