### Statistical analysis

All data analysis will be performed using SPSS Statistics v21.0 (IBM). To ensure that they are blinded to group assignment, the outcome assessors and data analysts will not interact with the participants except during data collection (in the case of outcome assessors). Demographic and other baseline characteristics will be summarized using descriptive statistics. If necessary, the results will be adjusted for potential confounders, such as age, gender, and education. Quantitative data will be expressed as frequencies or rates and statistical analysis will be carried out using the *χ*^2^ test. If these data are normally distributed, they will be expressed as (*x* ± *s*). The effects of the interventions (between-group differences) will be calculated with linear mixed models using interaction terms (group allocation versus time), which are equivalent to the between-group differences. The within-group differences will be calculated using repeated measures ANOVA. *P*-values < 0.05 will be considered statistically significant. The data will be reviewed before analysis. The Statistical Package for the Social Sciences (SPSS) software will be used for all analyses. The clinical relevance of the results will be confirmed by calculating the effect size (Cohen d) of the significant differences found between the assessments. The following effects will be considered: small: 0.00–0.49; medium: 0.50–0.79; high ≥0.80 (Cohen, 1988). Comparison between the four subgroups within the intervention group using ANOVA test.

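### Cohen d is calculated only for significant differences and then taken to confirm clinical relevance, a check that no result can fail and that inflates the reported effects

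*Protocol article*

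**What the plan says.** All of this is in the Statistical analysis section of the protocol article unless stated otherwise.

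- Significance: P-"values < 0.05 will be considered statistically significant". Sidedness is not stated.
- Effect size: "The clinical relevance of the results will be confirmed by calculating the effect size (Cohen d) of the significant differences found between the assessments".
- Grading: "small: 0.00–0.49; medium: 0.50–0.79", with high from 0.80 upwards.
- Tests: between-group effects come from the group-by-time term of a linear mixed model, and within-group change from repeated measures ANOVA. Adjustment for age, gender and education is possible.
- Primary outcomes (Primary outcomes section): MoCA and MMSE. No difference in points on either scale is named as important or unimportant.
- Size (Sample size calculation section): "A total of 68 participants will be needed, with 34 participants per group", and "Considering a 20% loss of follow-up rate, the final sample size is 86, with 43 participants per group".

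**The concern.** A check of clinical relevance is useful only if a statistically significant result could fail it. Here d is computed only for results that have already passed the P-value threshold, and no value of d leads to the conclusion that an effect is too small to matter. For a given sample size and design, d is also largely a rescaled test statistic. The step therefore presents significance a second time under the name of clinical relevance.

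The second problem is bias. In a small trial, the estimates that cross the significance threshold are on average larger than the truth. If d is reported only for those, the published effect sizes are systematically too large. The rule covers 15 outcomes (MoCA, MMSE, AVLT, SDMT, SAS, GDS, MUNSH, QoL-AD, GSES, SES, health literacy, DSCS, FBS, HbA1c, PBS), each measured at 12 and 24 weeks. Outcomes that miss significance, possibly including the primary ones, get no d under this rule. Anyone using the article's effect sizes to plan a later trial or pool results would start from a selected and inflated set.

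**Working it through.** **1. Can the check fail?** This needs no arithmetic. Entry to the check requires P < 0.05. The outputs are small, medium or high. No output means not clinically relevant, and no MoCA or MMSE difference is set as a benchmark. Every result that enters is confirmed, whatever the sample size or test.

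**2. Inputs for the inflation.**

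- Evaluable n of 34 per group, or 43 if nobody is lost. The dropout step reproduces: 34/0.8 = 42.5, rounded up to 43, and 2 × 43 = 86.
- The 34 itself does not reproduce from the stated inputs. The article says that "HbA1c scores in intervention and control group are 6.49 ± 1.59 and 6.97 ± 0.73, respectively". The difference is 0.48, the root-mean-square SD is √((1.59² + 0.73²)/2) = 1.237, and d = 0.48/1.237 = 0.39. At two-sided α 0.05 and 90% power this needs 140 per group; power at 34 per group is about 35%. That is a separate matter. Here 34 serves only as the evaluable n, and 0.39 as one plausible true effect.
- A smaller true d of 0.2 is my assumption, to show a range.
- Two-sided testing at 0.05 is assumed.

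**3. Unadjusted two-sample comparison.** The smallest significant value is |d| = t(0.975, 2n−2) × √(2/n).

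- n = 34: 1.997 × √(2/34) = 0.484
- n = 43: 1.989 × √(2/43) = 0.429

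Simulated trials (200,000 per setting), averaging |d| over the significant ones:

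| True d | n per group | Mean \|d\| if significant | Ratio to truth | Graded medium or high |
|---|---|---|---|---|
| 0.39 | 34 | 0.65 | 1.7 | 93% |
| 0.39 | 43 | 0.59 | 1.5 | 72% |
| 0.2 | 34 | 0.61 | 3.1 | 90% |
| 0.2 | 43 | 0.54 | 2.7 | 58% |

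**4. Closer to the planned test.** The group-by-time contrast can be approximated by comparing change scores between groups, with d in units of the raw SD. The smallest significant value becomes t × √(2/n) × √(2(1−ρ)), where ρ is the correlation between visits. The article gives no ρ, so I take 0.5 to 0.8. With 34 per group:

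| ρ | Smallest significant \|d\| | Mean \|d\| if significant, true 0.39 | Mean \|d\| if significant, true 0.2 |
|---|---|---|---|
| 0.5 | 0.484 × √1.0 = 0.484 | about 0.64 | about 0.59 |
| 0.7 | 0.484 × √0.6 = 0.375 | about 0.53 | about 0.47 |
| 0.8 | 0.484 × √0.4 = 0.306 | about 0.46 | about 0.39 |

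The ratio to the truth runs from 0.64/0.39 = 1.6 down to 0.46/0.39 = 1.2 for a true d of 0.39, and from 0.59/0.2 = 3.0 down to 0.39/0.2 = 2.0 for a true d of 0.2. The share of significant results graded medium or high at a true d of 0.2 falls from about 80% to about 10% across this range. The grading therefore depends heavily on ρ. The direction of the bias does not.

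**The case against.** The strongest reply is that the rule changes no test and no decision on the primary outcome. It adds a label to results that are analysed elsewhere. That is true, and it limits the weight of the point. It does not rescue the label, because the article says that the label establishes clinical relevance.

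A reader might infer that with 34 per group every significant difference must have d of at least 0.48, so that nearly all would be graded medium or high. The document does not support this. The 0.484 floor belongs to an unadjusted two-sample t-test, which is not the planned analysis. For the group-by-time term it drops below 0.48 once ρ exceeds about 0.5. For within-group change the paired floor at 34 is 0.349, and the phrase about differences between the assessments may well refer to time points. Even 0.484 lies inside the article's own small band, so a significant result can be graded small. The check cannot fail because no outcome of it means not relevant; the floor is not the reason.

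A reader might also infer that non-significant results will be withheld. The article restricts only Cohen d in this way. The mixed-model differences carry no such restriction, and confidence intervals and table layout may be set out in a fuller document. That part of the objection stands. It leaves the restriction on d itself untouched, since that is stated outright.

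Finally, the lower band starting at 0.00 has little practical consequence on its own: a d near zero would not be significant in a trial of this size and so would never be graded.

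**Conclusion.** The point holds. The article makes Cohen d conditional on significance and then treats it as confirming clinical relevance, with nothing that could count against relevance. This follows from the text alone and rests on no assumption.

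The inflation was present in every setting examined: between 1.2 and 1.7 times the truth for a true d of 0.39, and between 2.0 and 3.1 times for a true d of 0.2. These figures assume two-sided testing at 0.05 and 34 or 43 per group. For the planned contrast they also assume a change-score approximation with 34 per group, raw-SD units and ρ of 0.5 to 0.8. Different values would change the size but not the direction. The conclusion needs neither a universal minimum d nor any claim that most significant results will be graded medium or high.

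This should be corrected, because the stated rule biases the reported effect sizes. It does not threaten the validity of the primary test.

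**What to change.** In the Statistical analysis section:

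1. Report the between-group difference and Cohen d, each with a 95% CI, for every outcome at 12 and 24 weeks whatever the P value, and state which SD standardises d.
2. Judge the clinical relevance of the primary result by comparing the estimate and its CI with a difference on the MoCA/MMSE scale, fixed before the data are seen.
3. Delete the statement that d for significant differences confirms clinical relevance.

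The cost is a sentence in the analysis section and a few extra table columns. No new data are needed.

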Routine self-management often includes the use of offline educational materials such as health manuals and lectures. However, the Internet is not limited by space and time, which makes it an important tool for training and education. “Internet-assisted” medical treatment is being increasingly applied in nursing [26]. During the COVID-19 pandemic, this intervention has been used to optimize medical structures, dynamically monitor changes in patient conditions, and provide guidance for rapid rehabilitation [27]. Studies indicate that this has worked to effectively reduce the risk of viral spread and improve the efficiency of medical treatment [28]. Among numerous internet-assisted interventions, WeChat has become a commonly used social media software for Chinese researchers and patients, and many studies have adopted WeChat as a medium for internet-assisted self-management interventions, achieving positive results [29, 30]. It is worthwhile to evaluate the use of a stratified support pattern-based internet-assisted self-management therapy for DM-MCI with WeChat as the intervention medium. And randomized controlled trial (RCT), as an important method widely used in the clinical verification of intervention technology around the world, has been applied to the self-management research of more patients with mild cognitive impairment or diabetes patients [31]. Therefore, we will use RCT as the research design method to verify the effectiveness of stratified support pattern-based internet-assisted self-management therapy(SISMT) for DM-MCI.

The current study has designed a self-management intervention using the “Internet-assisted” stratified support-pattern may be able to consider the heterogeneity of patients more and provide them with more personalized intervention strategies. The aim is to use this approach to address the heterogeneous needs of patients with DM-MCI. Stratification was determined based on the cluster classification of patient cognitive function and self-management ability. Using these characteristics along with expert guidelines and consensus [32, 33], intervention measures will be implemented for a duration of 12 weeks. The effectiveness of the intervention on the self-management and cognitive function of each group of patients with DM-MCI will be explored.

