### Randomization, blinding, and concealed allocation

Ensuring allocation concealment, participants will be randomized (after obtaining written informed consent, eligibility screening, and baseline assessment) to the intervention and control groups at a 1:1 ratio by a study staff member (who will not be involved in participant recruitment or outcome assessment) using Research Randomizer software (http://www.randomizer.org/). Participants in the intervention group will be assigned to different categories of the intervention group based on their cognitive function and self-management characteristics and will receive Intervention measures with different frequencies. Participants in the control group will be assigned to different categories of the control group based on their cognitive function and self-management characteristics, too, but there is no difference in intervention frequency. The participants will then be told their group assignment by the intervention staff. Due to the nature of non-pharmacological interventions, only the outcome assessors and data analysts (not the participants or intervention staff) will be blinded to group allocation.

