### Intervention

#### Intervention group

In this study, the intervention group will adopt a SISMT. After the completion of the baseline survey, participants will formulate personalized intervention measures and optimize and expand their knowledge through hierarchical strategies to improve their self-management behavior. Based on our previous research in this study, the patients will be divided into four categories according to cognitive function and self-management ability: (1) high cognitive high management, (2) high cognitive low management, (3) low cognitive high management, and (4) low cognitive low management. Four WeChat groups will be formed to intervene separately to prevent communications between each category of participants in the intervention group. Self-management interventions targeted to patients with DM-MCI will be implemented, including diet, exercise, drug intake, psychology, and cognition. To achieve stratified intervention with different intensity, the content will remain the same for each group, but the frequency will differ. The intervention plan is shown in Table 1. All intervention content will be implemented through home self-monitoring and WeChat feedback. When patients experience suboptimal blood sugar monitoring, researchers will guide them in regulating self-management behavior. If behavioral regulation is ineffective, contact the attending physician for medication guidance. The outcome indicators will be collected at three time points: baseline, 12 and 24 weeks, respectively.

**Table 1 Tab1:** Intervention plan of the the stratified support pattern-based internet-assisted self-management therapy for DM-MCI

Patient type	Intervention method	Specific content

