#### Primary outcomes

The primary outcome measures will be general cognitive function (MoCA [35], MMSE [36]).

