#### Secondary outcomes

The secondary outcome measures will include several commonly used measures of specific domains of cognitive function, psychological indicators, blood glucose control (FBS, HbA1c, PBS) and other relevant indicators. The measures of specific domains of cognitive function (memory, language, attentions) will comprise the Auditory Verbal Learning Test (AVLT) [43], Symbol Digital Modalities Test (SDMT) [44]. Psychological status will serve as the secondary index of this study. This will include anxiety, depression, well-being, quality of life, self-efficacy, and self-esteem. The Self-Rating Anxiety Scale (SAS) will be used to measure anxiety [45] and the Geriatric Depression Scale (GDS) will measure depression [46]. Well-being will be assessed using the Memorial University of Newfoundland Scale of Happiness (MUNSH) [47]. Quality of Life-Alzheimer’s Disease (QoL-AD) will be used to assess patient quality of life [48], the General Self-efficacy Scale (GSES) will be used to measure self-efficacy [49], and the Self-Esteem Scale (SES) will be used to measure self-esteem [50]. Other relevant indicators include the healthy literacy and self-management behavior which can be used to investigate the patient’s acceptance of the intervention content. Health literacy and self-management behavior will be determined using the Health Literacy Scale for type 2 diabetes and the diabetes self-care scale (DSCS).

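### The four-class ANOVA inside the intervention arm cannot show whether benefit differs by class, and on the outcomes that define the classes (MoCA/MMSE, DSCS) it is likely to be significant with no intervention effect

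*Protocol article*

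**What the plan says.** All references are to the protocol article.

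- **The test** (Statistical analysis): "Comparison between the four subgroups within the intervention group using ANOVA test". No outcome, time point or scale (follow-up score or change) is named for it, and no adjustment for the baseline score. The section provides only for adjustment, where needed, for confounders such as age, gender and education.
- **The classes** (Intervention group): "the patients will be divided into four categories according to cognitive function and self-management ability", giving high or low cognition crossed with high or low self-management. The Background adds: "Stratification was determined based on the cluster classification of patient cognitive function and self-management ability". No cut-points or expected class sizes are given.
- **Timing** (Intervention group): "After the completion of the baseline survey, participants will formulate personalized intervention measures". Class is therefore a baseline characteristic.
- **Frequency** (Intervention group): "the content will remain the same for each group, but the frequency will differ".
- **Controls** (Randomization, blinding, and concealed allocation): "Participants in the control group will be assigned to different categories of the control group based on their cognitive function and self-management characteristics", with no difference in frequency between their classes.
- **Outcomes**: general cognition (MoCA, MMSE) is primary. Self-management on the DSCS is among the secondary outcomes.
- **Main comparison** (Statistical analysis): a linear mixed model with a group-by-time interaction. No class term is stated.

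**The concern.** The ANOVA compares people who were sorted into classes on the quantity being compared. On follow-up MoCA or DSCS, classes that differed at baseline will still differ at 12 and 24 weeks. On change from baseline, low scorers tend to rise and high scorers to fall without any treatment. Neither pattern says anything about the intervention. Frequency is also fixed by class, so inside this one arm a class difference cannot be separated from a frequency difference.

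The Background says, directly after describing the stratification, that effectiveness for self-management and cognition in each group of patients will be explored. The natural reading is effectiveness by class. The control participants who could answer that question are to be classified in the same way, but the analysis leaves them out. The Statistical analysis section applies a 0.05 threshold without marking this test as exploratory, so a class difference could be reported as a significant finding and read as differential benefit.

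**Working it through.** The article gives no figure for this ANOVA, so there is none to reproduce. The check is how often it rejects when the intervention has no effect.

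**Inputs from the article.** Four classes from two binary splits; alpha 0.05; 34 evaluable and 43 randomised per arm (Sample size calculation). The abstract's total of 84, or 42 per arm, gives nearly the same results as 43.

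**Assumed.** Standard normal baseline scores, a median split on each, equal variance at baseline and follow-up, and a baseline-to-follow-up correlation r. The outcome is the score that defines the class.

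**1. Why rejection is expected.** Under a median split of a standard normal score, the high and low halves differ at baseline by 2 × √(2/π) = 1.60 SD. With no intervention effect:
- the difference at follow-up is r × 1.60: 0.80 SD at r = 0.5 and 1.12 SD at r = 0.7;
- the difference in change, in the opposite direction, is (1 − r) × 1.60: 0.80 SD at r = 0.5 and 0.48 SD at r = 0.7.

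**2. Rejection rate of the ANOVA at 0.05, no intervention effect.** There were two sets of simulations: classifiers uncorrelated (6,000 trials per setting) and correlated 0.2 (2,000 trials per setting).

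| Scale | n in arm | r = 0.5 (corr. 0 / 0.2) | r = 0.7 (corr. 0 / 0.2) |
|---|---|---|---|
| Follow-up | 34 | 46% / 46% | 88% / 88% |
| Follow-up | 43 | 59% / 60% | 95% / 96% |
| Change | 34 | 47% / 49% | 27% / 29% |
| Change | 43 | 60% / 62% | 35% / 34% |

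At r = 0.8 (correlation 0.2), follow-up rejection is 98% to about 100% and change rejection 20–24%.

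**3. Other outcomes, follow-up score.** If the outcome correlates 0, 0.2 or 0.3 with baseline cognition, rejection is about 5%, 10–12% and 18–23%.

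**4. MoCA under the printed eligibility bands.** The Diagnosis criteria list MoCA 13–14, 19–20 or 24–25 by education. Read literally, these leave almost no baseline spread within a band, so high or low cognition largely follows education. Simulating those bands (assumed: follow-up centred on the person's own band, residual SD 1.5–2.5, three education mixes, n = 34 and 43) gives about 5–6% rejection on MoCA change and 95–100% on follow-up MoCA.

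**5. The alternative.** A class-by-arm interaction test over both arms, adjusted for the baseline score, rejects in 4–6% of null trials at every r (0 to 0.9) and n (34, 42, 43) tried.

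**The case against.** **No effect claim is attached to the ANOVA.** The article assigns intervention effects to the between-arm mixed model and calls this only a comparison between subgroups. If classes differ at baseline and the difference persists, the ANOVA's null of equal class means is false and rejecting it is correct. This stands: the follow-up percentages are not type I error rates of the ANOVA. They show how often a significant result arises without any intervention effect, so the error would lie in reading it as differential benefit.

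**Most outcomes are not classifiers.** Glucose measures, psychological scales and health literacy do not define the classes. A reader might infer that the test misleads on every outcome; step 3 does not support that.

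**The change-score rates may not apply to MoCA.** This stands if the bands are literal, although they may be abbreviated cut-offs. DSCS has no such restriction, so regression to the mean can still affect its change score.

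**No objective rests on it.** Every stated objective and hypothesis compares the two arms. A reader might infer that the trial's main conclusion is at risk; it is not, because the between-arm model does not use this ANOVA.

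**Baseline adjustment within the arm would be enough.** In the same simulations, adjusting the within-arm comparison for baseline brought rejection to 4–6%. It would still lack a control comparison and leave class confounded with frequency, so it could not show differential benefit.

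**Conclusion.** The point holds for the outcomes that define the classes. On follow-up MoCA/MMSE or DSCS, a significant class difference is expected with no intervention effect: about 46–95% of trials with 34 to 43 in the arm. On change scores it can arise from regression to the mean, in about 27–60%, but near 5–6% for MoCA if the eligibility bands are literal. These sizes rest on median splits and r between 0.5 and 0.7, neither of which the article gives. They also take MoCA/MMSE and DSCS as the classifying scores, since the article names only cognition and self-management. Inflation is smaller for outcomes weakly related to the classifiers and absent for unrelated ones.

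Whatever the outcome, a comparison confined to the treated arm cannot show whether benefit differs by class. The flaw is in an exploratory question and does not touch the primary or secondary between-arm comparisons. It is still worth correcting, because the data for a valid answer are already to be collected.

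**What to change.** Replace the ANOVA sentence with an arm-by-class (by time) term, adjusted for the baseline score, in the linear mixed model over both arms. State that class is assigned by one rule from T0 data in both arms. Baseline assessment already precedes randomisation and controls are already to be classified, so no new data are needed. Report the between-arm difference with its 95% CI in each class, labelled exploratory.

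The cost is a sentence or two in the analysis section. The randomisation procedure need not change; using class as a randomisation stratum would be a separate, optional design choice.

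The estimates will be imprecise. With equal class sizes (assumed) there are 43/4 ≈ 11 per arm per class, or 34/4 = 8.5 after dropout. The approximate 95% half-width is 1.96 × √(2/10.75) = 0.85 SD, or 1.96 × √(2/8.5) = 0.95 SD, before baseline adjustment. Adjustment multiplies this by √(1 − r²), giving about 0.60–0.82 SD for r from 0.7 to 0.5. The article calls 0.50–0.79 a medium effect, so absence of a detected class difference should not be read as equal benefit.
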